### Sample size calculation

2.4

This study is an exploratory investigation, with the primary outcome measure defined as the reduction in the monthly migraine days (MMD) from baseline after 4 weeks of treatment. As a novel acupuncture technique, Fu’s Subcutaneous Needling (FSN) inevitably lacks high-quality randomized controlled trials (RCTs) to inform sample size estimation. Therefore, reference is made to an internationally rigorous RCT on acupuncture for migraine without aura (23), and the sample size is estimated based on this study, combined with clinical FSN practice and the current study design. The hypothesis posited comparable effect sizes between the two interventions (FSN group and flunarizine hydrochloride group) in this trial and those observed in the prior study’s acupuncture and flunarizine hydrochloride groups. The referenced study reported that after 4 weeks of treatment, the MMD in the acupuncture group decreased by 4.1 ± 3.5 from baseline, while the MMD in the flunarizine hydrochloride group decreased by 1.9 ± 2.3 from baseline. To verify whether the efficacy of FSN is at least not inferior to that of flunarizine hydrochloride, a non-inferiority test is employed. Based on previous research (24), the most commonly selected non-inferiority margin for Monthly Migraine Days (MMD) in migraine studies is 1. The calculation is performed using the Non-Inferiority Tests for the Difference Between Two Means in PASS 15.0 software. With *α* = 0.05 (two-sided), power (1−*β*) = 0.9, and an anticipated 25%dropout rate, a total of 44 participants (22 per group, 1:1 ratio) are required to detect a statistically significant difference in MMD changes between the two groups.

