## Intervention

3

Before formal intervention, researchers record participants’ demographic and clinical characteristics, including gender, age, allergy history, marital and reproductive history, family history, smoking and alcohol consumption history, past medical history, medication history, and other relevant clinical data. Participants are educated on adherence to scheduled FSN sessions or flunarizine hydrochloride administration and instructed to avoid other migraine treatments that might interfere with efficacy assessment, such as oral analgesics, acupuncture, massage and so on. On study days, participants are advised to abstain from caffeine and alcohol and ensure adequate rest the night before.

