### FSN therapy

3.1

Participants are seated while the practitioner identify affected muscles (sternocleidomastoid, scalene, splenius capitis, and upper trapezius) via sliding palpation. The palpation reveal tissue tension, rigidity, firmness, and a smooth, resilient texture, accompanied by cord-like changes. The affected muscle tissues may exhibit localized soreness and discomfort. After disinfection, a disposable FSN needle (diameter 0.60 mm, length 50 mm; Nanjing Paifu Medical Technology Co., Ltd., Jiangsu, China) is inserted parallelly to the subcutaneous loose connective tissue surrounding the affected muscle. Once fully inserted, the soft tube stand is secured in the slot. The operator then perform alternating sweeping motions using the index and ring fingers with an angle of 60°at a frequency of 100 sweeps per minute. This is accompanied by reperfusion activities—resistance-based contraction and relaxation of the affected muscles, performed collaboratively by the practitioner and participant. After 20 sweeping dispersions, a 10-s reperfusion activity is performed, with this procedure repeated 3 times for each affected muscle. Reperfusion methods for specific muscles are as follows:

Sternocleidomastoid: seated, the participant turn the head toward the unaffected side while the practitioner apply resistance to the affected side, prompting the participant to attempt turning toward the affected side.Scalene: seated, the participant tilted the head slightly toward the affected side while the practitioner resist, prompting the participant to attempt further tilting.Splenius Capitis: seated, the participant extend the head maximally (until the line between the ear apex and earlobe was horizontal) while the practitioner resist at the occiput, prompting the participant to attempt further extension.Upper Trapezius: seated, the participant maximally elevate the affected shoulder while the practitioner resist, prompting the participant to attempt further elevation.

The FSN group receive treatment twice weekly for 4 weeks.

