### Oral flunarizine hydrochloride

3.2

Participants in the drug group are administered 5 mg flunarizine hydrochloride capsules nightly before sleep for 4 weeks and complete a medication monitoring form after each dose. After the 28th doses, participants will submit their medication monitoring forms to the investigators for review. Close follow-up will be conducted by the investigators during the medication period, and treatment will be immediately discontinued upon occurrence of any adverse events. If necessary, symptomatic treatment will be administered until the adverse events resolve.

Management of Missed Doses: a missed dose is defined as failure to administer the 5 mg dose within a 24-h period. Subjects are required to record each administration in their medication diary. If a dose is missed, no additional dose is to be taken to compensate; instead, the regular dosing schedule is to be resumed at the next planned administration time. All instances of missed doses are recorded in the diary and considered in the adherence analysis.

Study personnel review the medication diaries at each follow-up visit. Adherence is calculated as the percentage of actual doses taken relative to the total planned number of doses (28 doses). Subjects with an adherence rate below 80%were flagged for handling in the sensitivity analysis.

In cases of severe pain (VAS score >8), participants are permitted to take acute analgesic medication. In accordance with the Chinese Guidelines for Migraine Diagnosis and Treatment (25), ibuprofen sustained-release capsules are recommended for pain relief (one capsule per dose, no more than twice daily). If ibuprofen is ineffective, participants could take previously effective analgesics, with detailed records in headache diaries, including drug name, administration time, dosage, and time to headache relief after medication. Prophylactic migraine medications are prohibited.

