## Statistical analysis

6

Statistical analyses are conducted using SPSS 25. All tests employ two-sided comparisons, with statistical significance defined as *p* < 0.05.

Normally distributed continuous variables are presented as mean ± standard deviation (SD), whereas non-normally distributed variables are reported as median and inter-quartile range (IQR). Categorical variables appear as frequency and percentage (proportions).

For the MMD, MSQOL, MIDAS and VAS scale scores, between-group differences in changes from baseline to 4 weeks post-treatment are analyzed using either the independent *t*-test or Mann–Whitney U test, as appropriate. Intra-group comparisons between baseline and 4-week post-treatment measurements are conducted using paired *t*-test or Wilcoxon signed-rank test. Given the repeated measurements of MMD and the scale scores, repeated-measures analysis of variance (ANOVA) is additionally employed for supplementary analysis. For near-infrared spectroscopy (NIRS)-derived oxygen saturation levels, analyzed for within-group differences before and after treatment using paired *t*-test.

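### The 80% adherence flag that feeds the sensitivity analysis is defined by flunarizine doses only, so any analysis built on it would treat one randomised arm differently

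*Protocol article*

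**What the plan says.** The adherence rule stands in section 3.2 (Oral flunarizine hydrochloride) of the protocol article. Drug-arm participants take "capsules nightly before sleep for 4 weeks and complete a medication monitoring form after each dose". Adherence is then defined: "Adherence is calculated as the percentage of actual doses taken relative to the total planned number of doses (28 doses"). The next sentence gives it a use in the analysis: "Subjects with an adherence rate below 80%were flagged for handling in the sensitivity analysis".

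For the other arm, section 3.1 (FSN therapy) gives only the schedule: "The FSN group receive treatment twice weekly for 4 weeks". It states no attendance measure and no threshold. Section 3 (Intervention) does treat adherence as relevant to both arms, but only as instruction to participants: "Participants are educated on adherence to scheduled FSN sessions or flunarizine hydrochloride administration".

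Section 6 (Statistical analysis) says that "between-group differences in changes from baseline to 4 weeks post-treatment are analyzed using either the independent" t-test or its rank-based alternative. It names no adherence criterion and describes no sensitivity analysis. Section 2.4 sets the inferential frame: "a non-inferiority test is employed", with the margin taken from the statement that "the most commonly selected non-inferiority margin for Monthly Migraine Days (MMD) in migraine studies is 1".

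**The concern.** The article fixes a formula, a denominator, a cut-off and a purpose, and together these can pick out participants from the comparator arm only. An FSN participant who attends three of eight sessions carries no flag; a flunarizine participant who takes 22 of 28 capsules does.

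Incomplete treatment is foreseeable in both arms. Section 3.2 provides for stopping the drug when an adverse event occurs, and a participant who stops before the 23rd dose falls below 80%. Section 5 provides for FSN to be interrupted or stopped for larger haematomas, and nothing in the rule would register those missed sessions. Section 2.4 plans for 25% dropout.

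In a non-inferiority comparison, an adherence-based analysis is useful because poor adherence can make two treatments look more alike than they are. If the check re-handles participants in one arm and leaves the other whole, it no longer compares like with like, and a reader cannot tell whether a changed estimate reflects adherence or selection.

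**Working it through.** **Inputs**
- Planned doses: 28; threshold: 80% (section 3.2).
- FSN schedule: two sessions a week for 4 weeks (section 3.1).
- Arm size 22; assumed mean reduction in monthly migraine days 1.9 for flunarizine and 4.1 for FSN; margin 1 day (section 2.4).
- Not in the document, so assumed: the number of flagged drug participants k (2 to 4), their mean reduction m (0 to 3.8 days), and that flagged participants are excluded.

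**Step 1: the article's own denominator.** Nightly dosing for 4 weeks gives 7 x 4 = 28 doses, as stated.

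**Step 2: the cut-off in whole units.**
- Drug: 0.80 x 28 = 22.4. So 22 doses (78.6%) is flagged and 23 doses (82.1%) is not.
- FSN: 2 x 4 = 8 sessions and 0.80 x 8 = 6.4. Under the same rule 6 sessions (75%) would be flagged and 7 (87.5%) would not. The article contains no such rule.

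**Step 3: what one-sided exclusion could do.** The drug-arm mean after removing k participants with mean m is

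(1.9 x 22 - k x m) / (22 - k), where 1.9 x 22 = 41.8.

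| k | m (days) | Drug-arm mean | Shift from 1.9 |
|---|---|---|---|
| 2 | 0 | 41.8 / 20 = 2.09 | +0.19 |
| 2 | 1.9 | 38.0 / 20 = 1.90 | 0 |
| 2 | 3.8 | 34.2 / 20 = 1.71 | -0.19 |
| 4 | 0 | 41.8 / 18 = 2.32 | +0.42 |
| 4 | 1.9 | 34.2 / 18 = 1.90 | 0 |
| 4 | 3.8 | 26.6 / 18 = 1.48 | -0.42 |

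The shift runs from -0.42 through zero to +0.42 day. The FSN mean does not move, because nobody in that arm can be flagged.

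**Step 4: what that means for the comparison.** On the planning values the FSN advantage is 4.1 - 1.9 = 2.2 days. With k = 4 it becomes 2.2 - 0.42 = 1.78 if the excluded participants had not improved at all, or 2.2 + 0.42 = 2.62 if they had improved by 3.8 days. If non-adherers improve less than adherers, exclusion raises the drug-arm mean and works against FSN, which is conservative for the non-inferiority claim. If they improve more, the shift favours FSN.

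**The case against.** The strongest case against has three parts.

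- *Nothing says that flagged participants are removed.* They are marked for handling that is not described. It could be exclusion, a covariate, a separate listing or something else. This stands, and it is why the figures above are an illustration only.
- *The rule sits in the drug section of a condensed article.* A dose-based definition belongs there, and an FSN attendance rule or the content of the sensitivity analysis could be in the full protocol or SAP, which are not shown. This stands in part. The absence of those details is no fault. But the article does not leave adherence to another document: it states a measure, a threshold and an analytic use, and what it states can apply to one arm only.
- *The likely direction is harmless.* If non-adherent drug participants do worse, excluding them makes non-inferiority harder to show. That is a fair expectation but not an established one, and a conservative asymmetry is still an asymmetry.

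A reader might go further and infer that the plan filters one arm and so biases the trial's non-inferiority result. The document does not support that. It states no exclusion, and the between-group test in section 6 does not use the flag. A reader might also infer that non-inferiority should be claimed only if both an all-randomised and an adherent-set interval clear the margin. That would be a new decision rule for a trial that describes itself as exploratory, and this point does not require it.

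**Conclusion.** The point holds in a limited form. The adherence flag is defined for flunarizine only, cannot identify FSN participants who miss sessions, and would make any sensitivity analysis based on it one-sided. The primary comparison is untouched and the sample size of 44 does not change.

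Neither the size nor the direction of a distortion can be determined from the document. Under the stated assumptions (2 to 4 drug participants excluded, mean reduction 0 to 3.8 days) the drug-arm mean could move by about -0.4 to +0.4 day, zero included, against a margin of 1 day. This is a defect in a supporting analysis. It is worth correcting because the correction is cheap and, if made before the data are examined, removes later discretion over how FSN non-attenders are treated.

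**What to change.** Define adherence in both arms with the same 80% threshold: at least 23 of 28 doses for flunarizine and at least 7 of 8 sessions for FSN. State what the sensitivity analysis does with flagged participants, handle them identically in both arms, and report that analysis alongside the all-randomised result.

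The change to the text is about one or two sentences. Session attendance must be logged; the article does not say that it is, but the sessions are delivered by a practitioner and can be counted. Some FSN participants will also be flagged, so the adherent set becomes slightly smaller. With only eight sessions the threshold is coarse: missing two sessions is enough to be flagged, against six missed doses in the drug arm. The write-up should state this.

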## Outcomes

4

### Primary outcome

4.1

The change from baseline to the end of treatment (Day 28) in monthly migraine days (MMDs).

### Secondary outcomes

4.2

Migraine-Specific Quality of Life (MSQOL) scores, including three dimensions: functional limitations (the degree to which migraines limit daily activities), dysfunction (the avoidance of certain activities due to the concern of migraine attacks), and emotional impact (the effect of migraines on mood), assessed via 14 items on a 6-point scale (0–5). Scores are calculated for each dimension.Headache diaries, recording daily migraine episodes, including presence/absence of headache, frequency, average duration, and use of acute analgesics (if taken, drug name, dosage, and frequency were documented). The reduction rate in rescue medication use was extracted as an independent outcome measure, calculated as the percentage decrease in monthly medication frequency and dosage from baseline to the end of treatment and throughout the follow-up period.Migraine Disability Assessment (MIDAS): This score evaluates migraine-related disability through five items (including the number of days that work, household chores, and social/leisure activities are affected by migraine; the score ranges from 0 to 270, with higher scores indicating greater disability).The difference in Visual Analog Scale (VAS) scores from baseline at week 4 of treatment.

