#### Inclusion criteria

2.3.1

Meeting the diagnostic criteria for migraine without aura (MwoA) according to the International Classification of Headache Disorders, 3rd edition (ICHD-3) (1);Aged 18–65 years;A history of migraine for at least 1 year;At least 2 migraine attacks per month (meet the diagnostic criteria for migraine without aura (criteria B–D) as defined by ICHD-3);No prophylactic medications or other treatments for migraine within the past month;Visual Analog Scale (VAS) score >3;Voluntarily provided written informed consent.

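### Rescue-medication use is scored as a percentage decrease from baseline, which per participant has no value at zero baseline use, and the baseline month is not comparable with the on-study period

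*Protocol article*

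**What the plan says.** Within the secondary outcomes (section 4.2), the protocol article singles out one diary item: "The reduction rate in rescue medication use was extracted as an independent outcome measure". It fixes the formula as well: "calculated as the percentage decrease in monthly medication frequency and dosage from baseline to the end of treatment and throughout the follow-up period". The diary entry covers "use of acute analgesics (if taken, drug name, dosage, and frequency were documented"), so a month without any analgesic is a foreseen result.

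Four other places bear on what the baseline and on-study values can be:

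- Section 2.3.1 (inclusion) asks for "At least 2 migraine attacks per month" and "Visual Analog Scale (VAS) score >3". Neither this section nor section 2.3.2 requires any analgesic use.
- Section 2.3.1 also requires "No prophylactic medications or other treatments for migraine within the past month", and section 2.3.2 repeats this as an exclusion.
- Section 3 tells all participants to stay away from other migraine treatments during the study and gives oral analgesics as its first example.
- Section 3.2 makes an exception: "In cases of severe pain (VAS score >8), participants are permitted to take acute analgesic medication". It adds: "If ibuprofen is ineffective, participants could take previously effective analgesics".

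**The concern.** A percentage decrease needs a baseline that is above zero, not too small, and measured under the same conditions as the later value. The plan secures none of the three. Participants with no baseline use would have no score in a trial of 22 per arm, and those with one or two baseline uses would have scores that swing widely by chance. Separately, a fall from a baseline month to a month in which analgesics are restricted may partly reflect the restriction. At stake are whether this secondary outcome can be used and whether a within-arm reduction rate could be taken for a treatment effect.

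**Working it through.** The documents give no planning figure for rescue use, so there is none to reproduce. The only trial figure used is the total of 44 participants (section 2.4). Everything else below is an assumption and is marked as such.

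**1. Score at zero baseline.** With B uses in the baseline month and F in a later month, the score is 100 × (B − F)/B. At B = 0 it is undefined.

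**2. How many participants that could affect.** Expected number without a score = 44 × P(B = 0). Two assumed distributions are shown: Poisson, with P(0) = exp(−mean), and negative binomial with dispersion 1, with P(0) = 1/(1 + mean).

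| Assumed mean uses per month | Poisson P(0) | of 44 | Neg. binomial P(0) | of 44 |
|---|---|---|---|---|
| 1 | 0.368 | 16.2 | 0.50 | 22.0 |
| 2 | 0.135 | 6.0 | 0.33 | 14.7 |
| 3 | 0.050 | 2.2 | 0.25 | 11.0 |
| 4 | 0.018 | 0.8 | 0.20 | 8.8 |

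The range is about 1 to 22 of 44. Even if only 5% of participants have zero baseline use, the chance that at least one has no score is 1 − 0.95^44 = 0.90.

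**3. Instability at low baseline.** One extra or one fewer later use moves the score by 100/B points: 100 points at B = 1, but 10 points at B = 10. In a simulation with Poisson mean 2 in both months and no change in true use, the mean score among participants with B > 0 was about −15% (an apparent increase), and single values went as low as −900%.

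**4. Comparability of the baseline month.** The documents allow two readings.

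- *Analgesics were free in the baseline month.* Use then falls when the VAS > 8 rule starts, whatever the treatment does. For an upper bound, assume that every attack above VAS 3 was treated once at baseline, that only attacks above VAS 8 are treated on study, and that treatment has no effect. With attack VAS uniform on 3 to 10, the share above 8 is (10 − 8)/(10 − 3) = 0.286, a fall of 71%. With a normal distribution truncated to 3–10 (mean 5 to 7, SD 1.5 to 2), the share above 8 is 0.025 to 0.266, a fall of 73% to 98%. The fall is smaller if milder attacks went untreated at baseline.
- *The past-month bar covers analgesics.* Section 3 counts oral analgesics among other migraine treatments. If the bar in sections 2.3.1 and 2.3.2 has the same scope, baseline use is zero for every eligible participant. There is then no built-in fall, but all 44 scores are undefined.

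The per-participant score fails on either reading, for different reasons.

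**The case against.** The strongest reply is that section 4.2 does not name the unit of calculation. A group-level rate, 100 × (ΣB − ΣF)/ΣB within an arm, exists whenever the arm has any baseline use, and it excludes nobody. This is fair, but the section does not say that a group-level rate is meant. Such a rate would still carry any fall produced by the VAS > 8 rule, and it would still be undefined if analgesics were barred in the baseline month.

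A second reply is that the range in the table has no anchor. The planning figure in section 2.4, a mean fall of 4.1 migraine days, implies a mean baseline of at least 4.1 migraine days in that source population. If each day meant one use, the bottom row of the table would be the relevant one: about 1 to 9 participants. But migraine days are not analgesic uses, and the documents do not link the two. The uncertainty stands.

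A reader might also infer several stronger points that the documents do not support:

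- *Baseline use was unrestricted.* No section says so, and the eligibility bar can be read the opposite way.
- *Milligrams are summed across drugs, or a mean is dominated by light users.* Frequency and dosage are named separately and the drug name is recorded. Section 6 names no summary for this outcome and gives medians for skewed variables.
- *The check on the primary result is disabled.* Section 7 plans to compare recorded usage between groups, not the percentage score, and that comparison remains possible.
- *The restriction favours one arm.* The VAS > 8 rule stands under the flunarizine heading, but nothing says that it differs by arm.

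Finally, scoring a doubling from 1 and from 10 alike is a property of every relative measure and is not held against the plan here.

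**Conclusion.** The concern holds for one secondary outcome in a trial that calls itself exploratory. The formula is fixed in the protocol article. Per participant, it has no value at zero baseline use, which no criterion prevents, and it is unstable at low use. How many participants are affected cannot be known from the documents: about 1 to 22 of 44 under assumed means of 1 to 4 uses per month, and all 44 if the past-month bar covers analgesics.

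The built-in fall is conditional on analgesics having been free at baseline. Its 71% to 98% range is an upper bound under stated assumptions. If the restriction applies to both arms alike, it spoils within-arm readings and does not by itself bias the between-arm comparison. The raw diary data are kept, so the fault lies in the score and can be repaired without new data.

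**What to change.** Replace the percentage score in section 4.2 with the number of days (or uses) of acute analgesics per 28 days. Compare the arms at Day 28 and at each follow-up month with a model that includes the baseline value as a covariate, for example negative binomial (rate ratio) or ANCOVA (difference), with a 95% CI. Either choice gives a participant with zero baseline use a place in the analysis. Report doses by drug descriptively, and state that a within-arm fall is not to be read as a treatment effect.

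Reconcile sections 2.3.1, 2.3.2, 3, 3.2 and 4.2 on analgesic use before and during the study, so that it is clear what the baseline month can contain. Which rule applies is for the trial team; none is proposed here.

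The cost is a few lines of wording, using data the diaries already collect. The only loss is that the percentage figure is no longer reported.
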